##### Feasibility of the study design

We will collect information on the number of eligible participants and the percentage willing to participate in the study. Moreover, we will report the number of complete follow-up assessments and consider the study as feasible if at least 75% of the assessments will be completed.

#### Clinical outcomes

Primary outcome is the change in perceived stress level assessed by the German 10-item version of the PSS [66]. The PSS-10 assesses the unpredictability of, uncontrollability of, and state of being overwhelmed by daily life during the past week (exemplary item: “In the last week, how often have you been upset because of something that happened unexpectedly?”). The ten items are rated on a 5-point Likert scale (0 = *never* to 4 = *very often*). The ten items are summed up to receive a total score ranging between 0 and 40 with a higher total score representing a higher level of perceived stress. The PSS-10 has shown good reliability (Cronbach’s alpha = 0.84) and validity [66].

Secondary outcomes are symptoms of depression, emotion regulation skills, current stress level, stress-related (dys-)functional beliefs, emotional state, performance measures, and physiological stress measures.

*Symptoms of depression* will be assessed with the German version of the Center for Epidemiological Studies Depression Scale (CES-D; German version: [75]). The CES-D is a 20-item self-report questionnaire assessing the frequency of symptoms of depression in the general population during the last 7 days on a 4-point Likert scale (0 = *some of the time* to 3 = *most of the time*). The total score computed as the sum of all items can range between 0 and 60. Total scores higher than 22 are considered to indicate a clinically relevant depressive symptom severity [75]. The CES-D has shown good reliability (Cronbach’s alpha = 0.89–0.92) and validity in non-clinically depressed samples [76, 77].

*Emotion regulation skills* will be assessed with the Prolonged-State-Version of the Emotion Regulation Skills Questionnaire (ERSQ; German version: [78]). The self-report questionnaire measures the successful application of nine emotion regulation skills during the past week: *awareness* (e.g., “I paid attention to my feelings”), *sensations* (e.g., “My physical sensations were a good indication of how I was feeling”), *clarity* (e.g., “I was clear about what emotions I was experiencing”), *understanding* (e.g., “I was aware of why I felt the way I felt”), *modification* (e.g., “I was able to influence my negative feelings”), *acceptance* (e.g., “I accepted my emotions”), *tolerance* (e.g., “I felt I could tolerate my negative feelings”), *readiness to confront distressing situations* (e.g., “I did what I had planned, even if it made me feel uncomfortable or anxious”), and *self-support* (e.g., “I supported myself in emotionally distressing situations”). The 27 items are rated on a 5-point Likert scale (0 = *not at all* to 4 = *almost always*). In addition to the subscales assessing the specific emotion regulation skills, a general indicator of emotion regulation ability can be computed as the average score across all items (range = 0 to 4) with a higher score indicating higher emotion regulation skills. A number of studies demonstrated acceptable to good reliability (Cronbach’s alpha = 0.89–0.97) and validity of the questionnaire (e.g., [78–84]).

The *current stress level *will be assessed before each training session with a self-constructed short stress measure consisting of two items rated on an 11-point Likert scale (0 = *not at all* to 10 = *very much*): “Please indicate how stressed you feel at the moment” and “Please indicate how well you can cope with the stress at the moment.” The items will be analyzed separately.

To assess *stress-related (dys-)functional beliefs*, a total of ten items were selected from Rojas and colleagues’ [69] short version of the DAS. The DAS was developed as a self-report instrument to assess dysfunctional attitudes that are typically found in depressive patients. The ten items with the best fit for the stress context of the current study were selected by an expert group under supervision of MB: nine statements consisting of dysfunctional attitudes and one of a functional attitude. Then, two versions of the scale were created. The first version assesses the agreement with the ten DAS items on a 7-point Likert scale (DAS-A; 1 = *fully disagree* to 7 = *fully agree*) and the second version the perceived helpfulness of the beliefs (DAS-H; 1 = *not at all helpful* to 7 = *very helpful*). To obtain a total score, the functional-belief item is reversely coded, and the ten items are summed up. The total score in both versions ranges between 10 and 70. A higher score in the DAS-A represents higher agreement with dysfunctional stress-related beliefs, and a higher score in the DAS-H represents a higher helpfulness rating of dysfunctional beliefs.

To assess the *emotional state*, i.e., the intensity of emotions experienced during the last week, a team of experts in the assessment and regulation of emotions extended the German version of the Positive and Negative Affect Schedule [85] in a way that the following affective states are all assessed with one item: courage, gratitude, joy, pride, excitement, resolve, anger, anxiety, sadness, confidence, disgust, tranquility, love, happiness, relaxation, and content. Each item starts with the instruction “During the last week, I felt…” and invites participants to rate the intensity of the respective emotion during the past week on a 5-point Likert scale ranging from 0 = *not at all* to 4 = *very much*. The items will be analyzed separately.

#### Performance measures

The quality of participants’ emotion expression will be evaluated by the present investigator after each display of an emotion. The display in face, voice, and body will be rated on a 6-point Likert scale (0 = *no expression of the respective emotion* to 5 = *very strong expression of the respective emotion*). Moreover, participants will be asked to self-rate the felt intensity of the respective emotion after each stimulus on a visual analog scale presented on the smartphone (0 = *not at all* to 100 = *very much*). The smartphone app will also record the percentage of incorrect responses (expressing the wrong emotion in the eAAMT or swiping in the wrong direction in the swipe-based AAMT) as well as task completion time for all responses.

#### Physiological stress measures

To gain additional insights into the effects of the training on physiological stress systems, we will assess the concentration of hormonal stress markers as well as heart activity and respiration. Saliva samples for the assessment of cortisol and salivary alpha-amylase will be taken at the first and last training session before the training.

We will use Salivettes (Sarstedt, Nümbrecht, Germany) to collect the samples. The saliva samples will be analyzed at the Department of Health Psychology of the Friedrich-Alexander-Universität Erlangen-Nürnberg.

Heart activity and respiration will be recorded for 3.5 min in a subset of participants on day 1 and day 4 before and after the training. For this purpose, we will use a highly sensitive radar system, allowing for a contactless monitoring of the parameters of interest. For more details on the method, see [86]. Previous studies demonstrated the radar system to be a reliable and valid method for assessing heart activity and respiration in healthy individuals [87, 88]. We will be able to derive information on heart rate variability and breathing rate from these measurements.

#### Demographic information

We will also collect demographic data of the participants. Demographic data will include gender, age, education, current occupation, studies (degree, subject, semester), relationship status, psychotherapy (former and current), smoking, and medication.

### Procedures

Participants will be recruited via postings in social networks, the email newsletters of the Friedrich-Alexander-Universität Erlangen-Nürnberg, and flyers posted on notice boards in public places in Erlangen. The recruitment posts will provide interested individuals with a QR code and a link to the web site Unipark [89] where they will be informed about the study and will be given the opportunity to provide consent for participating in the first assessment. In case of informed consent, participants will be forwarded to the assessment of the inclusion and exclusion criteria. Individuals suitable for study inclusion will be randomized to one of the eight study conditions by the experimenters according to the randomization list. Neither participants nor experimenters will be blinded to the assignment.

During the training, the smartphone will record participants’ display of emotions with the integrated front camera. The recordings will be used as training material to train algorithms in automated emotion recognition (conducted in cooperation with the Chair of Embedded Intelligence for Healthcare and Wellbeing at the University of Augsburg and the Machine Learning and Data Analytics Lab at the Friedrich-Alexander-Universität Erlangen-Nürnberg). We will also record participants’ emotional expression with an external video camera and microphone. All of the video and sound recordings will only be used for training the algorithms and not be analyzed otherwise.

The clinical outcomes will be assessed at three time points via the web-based assessment tool Unipark [89]: directly before the training (T1), directly after the training (T2), and 1 week after training completion (T3). Feasibility outcomes will be assessed at T2. Additionally, participants in the intervention and swipe control groups will receive short daily questionnaires in paper–pencil format. Participants who do not fill out the T3 assessment will be reminded twice via email. In addition, participants who discontinue the intervention will be asked to answer the assessments anyway. Participants will be offered the opportunity to receive information about the results of the study via email.

Participants studying psychology will receive course credits for participation. Additionally, all participants enrolled in the study until May 2021 will have the chance of winning 500 € in a draw. From June 2021 onwards, participants will be offered an expense allowance of 20 € with psychology students having the choice between course credits and financial reimbursement. We undertook this change in procedure to compensate for COVID-19 associated problems with the recruitment.

### Ethical aspects

The study will be conducted following the Declaration of Helsinki and was approved by the German Psychological Society’s ethics committee ([name]2020-09-10AM). All modifications of the study protocol will be amended at the ethics committee and documented in the trial register.

In the online screening questionnaire, we will collect demographic information (see above) as well as participant’s email addresses to be able to inform them about further proceedings in the study. Moreover, the online-platform Unipark logs IP addresses, date, time and content of the request, and device information (e.g., operating system and version, app version). Concerning data privacy, the platform Unipark complies with the European Union’s General Data Protection Regulation [90]. After the online screening, each participant will receive an ID number, and any identifying information (i.e., email address, name on the consent form) will be stored separately from the data collected in the study. A list in hard copy joining ID numbers and email addresses will only be accessible to the principal investigator. All data collected in the study (i.e., questionnaire, physiological, and smartphone data, video and sound recordings) will be stored on an external disk only accessible for persons directly involved in the study. The final data set including questionnaire, physiological, and smartphone data will be anonymized and made available in the Open Science Framework.

### Statistical analysis plan

Before conducting the analyses, we will test the preconditions and in case of violations use alternative methods. The level of significance will be set to *α* = 0.05. We will report *p*-values for all analyses.

Feasibility outcomes will be analyzed with descriptive statistics and independent *t*-tests to compare the results of the eAAMT conditions with the swipe control condition. To gain insight into the differences in clinical outcome measures between study conditions, we will compute pre-post effect sizes. In addition, we will conduct exploratory analyses using two-way mixed analyses of variance (ANOVAs) with treatment as between-subjects factor and time as within-subjects factor. Because omnibus tests fail to detect differences between single conditions if the majority of conditions do not differ, we plan to run pairwise comparisons comparing the single eAAMT conditions with the inactive control condition and the swipe control condition. In order to prevent alpha-error accumulation, we will first compare the eAAMT conditions to the inactive control condition. Only if the interaction effect in this comparison will be significant, we will also compare the eAAMT conditions to the swipe control condition. Moreover, as this is a pilot trial and we aim to evaluate if the training is effective in itself, we will conduct per protocol analyses. We will also run intention-to-treat analyses to determine the robustness of the results when considering missing data. All analyses will be conducted in R [91] and SPSS.

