## Methods

### Design

We will conduct a parallel eight-armed randomized controlled pilot study (see Fig. 1 for the study flow and supplemental materials for the spirit checklist of the trial). The study will be conducted at the Department of Clinical Psychology and Psychotherapy of the Friedrich-Alexander-Universität Erlangen-Nürnberg. In the eAAMT and swipe control groups, participants will receive four sessions à 20–30 min of training on four consecutive days, while the inactive control group will not receive any training. Participants will be randomly assigned to one of the eight study groups with a 1:1 allocation. A postdoctoral researcher not otherwise involved in the study will generate a randomization list using random numbers in Microsoft Excel. A block randomization will be performed with a block size of eight. The study is registered in the German Clinical Trials Register (Deutsches Register Klinischer Studien; DRKS00023007).

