### Participants

Inclusion criteria for participation in the pilot study will be the following: (1) heightened levels of perceived stress as indicated by a score of 19 or above on the Perceived Stress Scale-10 (PSS-10; German version: [66]), (2) at least 18 years of age, and (3) ability and willingness to provide informed consent. Following procedures suggested by Heber and colleagues [67], the PSS cut-off score is set at one standard deviation above the PSS mean score in the validation study of the German version of the PSS-10 [66]. Exclusion criteria will be as follows: (1) the presence of a severe psychological condition (i.e., psychosis; based on self-report), (2) physical conditions impairing the expression of emotion (e.g., facial paralysis), (3) heavy smoking (i.e., more than 10 cigarettes/day due to possible confounding influences on cortisol measures), and (4) suicidal ideation. We expect a medium to large effect size based on previous smartphone-based AAMT studies (e.g., [52, 53]). Therefore, we will include *n* = 10 participants per study group (i.e., *N* = 80 in total) as suggested by Bell and colleagues [68] for pilot studies with expected medium to large effect sizes. To complete the intervention per protocol, participants should attend at least three of the four training sessions. To ensure even distribution of subsample sizes across study conditions, we will change randomization block size in case of treatment dropouts. Number of and reasons for dropping out will be recorded and reported for each condition.

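### Assumption tests on arms of about 10 choose the analysis method; they are unreliable at that size, and methods fixed in advance would do better at almost no cost

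*Protocol article*

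**What the plan says.** The Statistical analysis plan section opens with a two-stage rule: "Before conducting the analyses, we will test the preconditions and in case of violations use alternative methods". It continues: "The level of significance will be set to *α* = 0.05", with p-values to be reported for every analysis.

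The rule covers three sets of analyses:

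- Feasibility outcomes, by descriptive statistics and "independent *t*-tests to compare the results of the eAAMT conditions with the swipe control condition".
- Clinical outcomes, after pre-post effect sizes: "we will conduct exploratory analyses using two-way mixed analyses of variance (ANOVAs) with treatment as between-subjects factor and time as within-subjects factor".
- Arm pairs: "we plan to run pairwise comparisons comparing the single eAAMT conditions with the inactive control condition and the swipe control condition". The swipe comparison is made only if the interaction against the inactive control is significant.

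The cell sizes follow from three other statements:

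- Participants: "we will include *n* = 10 participants per study group (i.e., *N* = 80 in total").
- Design: "Participants will be randomly assigned to one of the eight study groups with a 1:1 allocation".
- Procedures, on the clinical assessments: "directly before the training (T1), directly after the training (T2), and 1 week after training completion (T3").

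**The concern.** A pretest helps only if it finds the violations that matter and stays quiet otherwise. With 10 observations it does neither well. It has little power against moderate skew or unequal variances. Repeated over many cells, it also raises false alarms. Two outcomes with the same underlying behaviour could then be analysed by different methods for chance reasons. The error rate of the whole procedure (pretest plus chosen test) is also no longer that of either test alone.

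Two things are at stake. One is the nominal 5% level of the eAAMT-versus-swipe feasibility t-tests. The other is the clinical swipe comparison, which is made or skipped on a significance result that may come from whichever method the pretest happened to select.

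**Working it through.** **Inputs from the article.** Eight arms, 10 per arm, three assessments of the questionnaire outcomes, alpha 0.05. The plan's total reproduces: 8 × 10 = 80.

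**Assumed inputs.** The article names no pretest, level or fallback. The check takes Shapiro-Wilk for normality and Levene for variances, each at 5%, and two-sided main tests. Mann-Whitney is used if normality fails, Welch if only Levene fails, and Student's t otherwise. Error rates come from simulated two-group comparisons at a single time, not from the full interaction test.

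**Step 1: how often the rule triggers when nothing is wrong.** For k independent tests at 5%, P(at least one flag) = 1 − 0.95^k.

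| What is tested for normality | k | Formula |
|---|---|---|
| One arm pair, 2 arms × 3 times | 6 | 26.5% |
| Feasibility ratings, 7 arms × 1 time | 7 | 30% |
| Saliva markers, 7 arms × 2 times (Table 1: not in the inactive arm) | 14 | 51% |
| Questionnaires, 8 arms × 3 times | 24 | 71% |

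Simulation with within-person correlation 0.3 to 0.7 gives 25–27% for 6 cells and about 70% for 24. Adding Levene and Mauchly gives about 37% for an arm pair and 73–74% for all eight arms. If normality is tested on pooled residuals, with Levene and Mauchly, the figure is 23–28%.

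**Step 2: how often a real violation is found.**

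- Shapiro-Wilk, n = 10: lognormal with log-SD 0.5, 25%; gamma with skew 1, 14%; gamma with skew 2, 44%.
- Levene (median-centred), 10 v 10: SD ratio 1.5, 13%; SD ratio 2, 31%.

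**Step 3: type I error of the whole rule against Welch used from the start.**

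| Setting | Test-then-switch | Welch always |
|---|---|---|
| 10 v 10, normal, equal SD | 4.9% | 4.7% |
| 10 v 10, SD ratio 2 | 5.6% | 5.0% |
| 10 v 10, skew 1 | 5.2% | 4.6% |
| 10 v 10, skew 2 | 5.2% | 3.8% |
| 10 v 7, smaller arm has twice the SD | 7.5% | 5.0% |
| 60 v 10, smaller arm's SD 1.5 times larger | about 10% | about 5% |
| 60 v 10, smaller arm's SD 2 times larger | about 9% | about 5% |
| 60 v 10, larger arm's SD 1.5–2 times larger | 3.0–4.5% | about 5% |

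The 60 is six eAAMT arms × 10. Student's t with no pretest has 14–22% error in the two unfavourable 60 v 10 settings, so the rule repairs part of the problem but not all of it. In the first 10 v 10 row, where there is nothing to correct, the method still switches in 13% of comparisons.

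**The case against.** The strongest reply has five parts.

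- **Chance triggering.** A reader might infer that the rule fires by chance in most outcomes. That needs a 5% normality test in every one of 24 cells, with a single failure enough to switch. The article does not say so. It plans arm-pair comparisons because it expects the omnibus test to miss differences, so the figure of about a quarter is at least as relevant. This stands.
- **Error rates.** A reader might also infer that the 5% level is generally broken. At the planned 10 v 10 with one violation it is not. Missing an SD ratio of 2 there does almost no harm. The 60 v 10 inflation needs pooling, which the text does not settle, and a larger SD in the swipe arm, which nothing in the article supports. In the other direction the rule is conservative. The text does not require the equal-variance t-test either. The 10 v 7 case is likewise assumed: per-protocol losses could produce it, but the article plans to adjust block size after dropouts to keep arms even. All of this stands.
- **Consequence.** Adherence, technical problems and assessment completion are judged by proportions, not by t-test p-values. The ANOVAs are called exploratory, and the article concedes that the sample is very small. This stands and limits the importance of the point.
- **Sphericity.** The sentence is the only provision for it. Deleting it without a replacement would do harm: with assumed correlations of 0.3/0.3/0.8 or 0.5/0.5/0.8 among the three times, the uncorrected interaction test at 10 v 10 has error of 6.9% or 6.0%. This stands, and the fix must cover it.
- **Detail left elsewhere.** Names of tests and fallbacks may sit in a separate analysis plan, so their absence is no fault. This is right, but it does not answer the point. The article commits to test-then-switch, and naming the tests would only carry that rule out.

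**Conclusion.** The point holds in a limited form. The stated rule lets unreliable pretests choose the method. Under the assumed tests, false alarms occur in roughly a quarter of arm-pair analyses and in up to about 70% of outcomes under full cell-by-cell testing. About three quarters of moderately skewed cells go unnoticed.

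The cost in type I error is nil to slight for equal arms with one violation. It is about 7–8% for 10 v 7 with an SD ratio of 2, and 9–10% for the pooled comparison when the swipe SD is larger. These figures depend on the pretests, fallbacks, distributions and SD ratios assumed above. The documents do not support a claim that the rule triggers in most outcomes whatever is tested, or that it generally exceeds 5%.

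The change is worth making because a better rule costs almost nothing and the swipe comparison depends on a significance result. It is not a threat to the trial's main purpose as a pilot.

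**What to change.** Replace the sentence with methods fixed in advance:

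- **Feasibility ratings and scores, eAAMT versus swipe:** Welch's t-test throughout. Keep adherence and technical problems as proportions and analyse them as such.
- **Cortisol, alpha-amylase and completion time:** log-transform in every case. This assumes right skew, as is usual for positive concentrations and times.
- **Other clinical outcomes:** keep the mixed ANOVA, with a Greenhouse-Geisser correction applied always and not after a sphericity test.
- **Diagnostics:** residual plots, for description only.
- **Alternatives:** report any other method, such as a permutation p-value, as a sensitivity analysis run whatever the diagnostics show.

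This changes wording only and needs no new data. The price is a small loss of power when variances are equal or sphericity holds.

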### Purpose of the study

Before conducting a large RCT on the eAAMT, we aim to test intervention and study procedures and estimate preliminary effect sizes on clinical outcomes. For this purpose, we will run a pilot study with the following aims: (a) evaluate the feasibility of the intervention and study design and (b) explore its efficacy in influencing clinical outcomes when compared to an inactive control condition and a swipe-based AAMT (swipe control condition). Additional exploratory questions are whether the specific emotions anxiety, anger, sadness, and disgust differ with respect to their effectiveness in eAAMTs and whether deviating from the common 50:50 ratio of approach vs. avoidance responses (e.g., [35, 47]) in favor of a 1:4 bias towards approach responses would lead to stronger effects on the reduction of perceived stress.

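### The listed comparisons set each eAAMT arm against the two controls only, so the emotion and ratio questions have no matching contrast, and the one named effect size is pre-post

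*Protocol article*

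**What the plan says.** All references are to the protocol article.

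- **Questions.** Purpose of the study asks, as an additional exploratory question, "whether the specific emotions anxiety, anger, sadness, and disgust differ with respect to their effectiveness in eAAMTs". It also asks whether a 1:4 bias towards approach responses reduces perceived stress more than the usual equal split. The Interventions section gives these two questions as the reason for having several eAAMT variants and introduces two arms specifically to study the ratio. The Discussion repeats both.
- **Effect size.** The Statistical analysis plan states: "To gain insight into the differences in clinical outcome measures between study conditions, we will compute pre-post effect sizes". No other effect size is named.
- **Tests.** The same section then plans two-way mixed ANOVAs (treatment between subjects, time within subjects). It warns that an omnibus test can miss differences between single conditions, and for that reason "we plan to run pairwise comparisons comparing the single eAAMT conditions with the inactive control condition and the swipe control condition". The swipe comparison follows only if the interaction against the inactive control is significant.
- **Outcome and size.** "Primary outcome is the change in perceived stress level assessed by the German 10-item version of the PSS". On size, "we will include *n* = 10 participants per study group (i.e., *N* = 80 in total").

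**The concern.** Six of the eight arms exist to compare emotions or ratios, yet the enumerated pairwise comparisons all have a control on one side. An eight-arm omnibus interaction, if fitted, would touch both questions but isolate neither, and the plan itself concedes this weakness of omnibus tests.

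The pre-post effect size does not fill the gap. On its natural reading it is a within-arm quantity. It therefore includes time trend, expectation effects in unblinded participants, and whatever regression to the mean remains between T1 and T2 after entry at a PSS-10 of 19 or more at screening.

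The pilot is meant to inform a larger RCT. If a reader takes the emotion or ratio answer from which arm beat control, or from which arm has the largest pre-post effect, the choice carried forward may rest largely on noise.

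**Working it through.** **Inputs from the article.** Ten per arm and equal allocation ("Participants will be randomly assigned to one of the eight study groups with a 1:1 allocation"); "The level of significance will be set to *α* = 0.05"; and "We expect a medium to large effect size based on previous smartphone-based AAMT studies", with no number given.

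**Assumptions.** Two-sided testing; d = 0.5 to 0.8 for medium to large; pre-post correlation r = 0.5 to 0.7, which the article does not give. The scale is the SD of PSS-10 at one time point, with one pre and one post measure.

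**1. The plan's own figure.** 8 arms × 10 = 80, which agrees. No power calculation is stated, so there is nothing further to reproduce.

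**2. Questions against comparisons.**
- Listed: 6 eAAMT arms × 2 controls = 12 pairwise comparisons.
- Needed for the emotion question: 6 pairs, or one 3-df contrast. Listed: none.
- Needed for the ratio question: 1 contrast. Listed: none.

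**3. Chance spread among four identical arms.** The variance of change is 2(1−r), so the SE of an arm's mean change is √[2(1−r)/10]. The expected range of four independent normal means is about 2.06 SE.

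| r | SE of arm mean | Expected best-minus-worst |
|---|---|---|
| 0.5 | √0.10 = 0.316 | 0.65 SD |
| 0.6 | √0.08 = 0.283 | 0.58 SD |
| 0.7 | √0.06 = 0.245 | 0.50 SD |

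**4. Reading the answer from significance against control.** Four arms with the same true effect were simulated against one shared inactive control, using a t-test on change with 18 df for each comparison. The table gives single-comparison power, then the share of trials in which some but not all four arms are significant.

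| r | d = 0.5: power; split | d = 0.8: power; split |
|---|---|---|
| 0.5 | 18%; 39% | 40%; 58% |
| 0.6 | 22%; 44% | 47%; 60% |
| 0.7 | 28%; 50% | 59%; 59% |

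Any two identical arms disagree on significance against control in 21% to 33% of trials. If within-arm pre-post significance is used instead, they disagree in 29% to 49%.

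**5. Baseline adjustment.** Change-score variance is 2(1−r) and ANCOVA variance is 1−r², so their ratio is (1+r)/2. At r = 0.6 this is 0.64/0.80 = 0.80, or 20% lower; it is 25% lower at r = 0.5 and 15% lower at r = 0.7.

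95% CI half-width for a 10 v 10 contrast at r = 0.6:
- change score, error pooled over eight arms (72 df): 1.99 × √(0.80 × 0.2) = 1.99 × 0.400 = ±0.80;
- change score, two arms only (18 df): 2.10 × 0.400 = ±0.84;
- ANCOVA, pooled (71 df): 1.99 × √(0.64 × 0.2) = 1.99 × 0.358 = ±0.71.

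Estimating the slope inflates the ANCOVA variance by about 1/(18−2) = 6% in a two-arm fit and 1/(72−2) = 1.4% in an eight-arm fit.

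Single-comparison power at d = 0.8 and r = 0.6 goes from 47% (change, 18 df) to 60% (ANCOVA, 71 df). About 3 of those points come from pooling the error term rather than from adjustment.

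**The case against.** The strongest reply is that the section already compares arms properly. A treatment-by-time interaction is a between-arm difference in change, and time trend and regression to the mean common to the arms cancel in it. This stands. A reader might infer from the pre-post sentence that arm differences will be read only from within-arm effect sizes, but the sentences after it show otherwise.

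Three further inferences go beyond the text:
- **A selection rule.** Nothing says the emotions or ratios will be ranked by significance or by the largest effect. The split rates show what such a reading would do, not what the plan prescribes.
- **Sizing the RCT on a within-arm figure.** The article says only that preliminary effect sizes will be estimated. It also does not define the pre-post effect size as within-arm, so a controlled form is not excluded.
- **Separate two-arm fits.** The section does not say whether the pairwise comparisons are separate models or contrasts in a larger one.

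It is also fair that a mixed ANOVA is valid in randomised arms and uses baseline through the time factor, so preferring ANCOVA is a point of efficiency. The questions are labelled exploratory, and the Discussion admits that the sample is very small.

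One might add that a condensed article leaves contrasts to a fuller plan. That has less force here, because the section does enumerate its pairwise comparisons and the enumeration omits the ones its own questions need.

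**Conclusion.** The point holds as a mismatch between stated questions and listed comparisons: neither the emotion question nor the ratio question is answered by any specified contrast. To say that they go wholly unanswered would be too strong, since an omnibus interaction and side-by-side description bear on them loosely.

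The listed tests cannot stand in for the missing contrasts. Identical arms would look different in about 40-60% of trials, with a chance spread of 0.50-0.65 SD. These figures rest on 10 per arm, d of 0.5-0.8, an assumed r of 0.5-0.7 and, for the split rates, 18-df tests.

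The missing baseline adjustment is a secondary loss of precision that depends on r, and is not an error. With or without it, a half-width of roughly 0.7-0.8 SD at r = 0.6 means the added contrasts will be estimates with wide intervals. The change is worth making before analysis; it does not affect the validity of the planned comparisons with the controls.

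**What to change.** In the Statistical analysis plan:

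1. Add a 3-df contrast (treatment by time, or its baseline-adjusted equivalent) among the four single-emotion arms, with the six pairwise differences and 95% CIs.
2. Add the 1:4 minus 1:1 difference with its 95% CI.
3. Label both as exploratory estimates, without claims of significance, and state that differences between eAAMT arms will not be inferred from which arm is significant against a control.
4. Report between-arm differences, raw and standardised, with 95% CIs as the effect sizes for planning the RCT, preferably from one model over all eight arms adjusted for T1 PSS-10.
5. Define the pre-post effect size and, if it is within-arm, keep it as description only.

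The cost is wording and contrast code. T1 PSS-10 is already collected in every arm, including the inactive control, so no new data are needed. Recruitment was still under way according to Trial status, so the change could be recorded in the trial register before analysis.
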